**Methods:**

A theory-based multicomponent intervention known as Program to Lower Unwanted Media Screens (PLUMS) at the household level has been developed. It is based on the social cognitive theory for children and self-determination theory for caregivers. After pretesting, a randomized control trial will be conducted to assess this intervention's effectiveness among healthy children aged 2-5 (±3 months) years and their primary caregivers who have at least one digital media gadget at home in zone three of Chandigarh (population of 2,730,035). A sample size of 428 children is estimated per arm. PLUMS includes disseminating specific information, education, communication in the form of videos and posters to the primary caregivers, and conducting motivational interviewing as and when needed. Children will be provided suggestions for playful activities as alternatives to digital media gadgets. The primary outcome is the mean change in the duration of screen time, and secondary outcomes are sleep duration and patterns, emotional-behavioral problems, and level of physical activity of the children. Per-protocol and intention-to-treat analyses will be conducted using SPSS for Macintosh, Version 25.0.

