#### Sample Size

The sample size for the individual level randomization was estimated using the following formula [38]: n_I_= (σ_1_^2^+σ_2_^2^) (Z_1-α/2_+ Z_1-β_)^2^/Δ^2^, where n = sample size, σ_1_ = standard deviation of the control group and assumed to be 2.09 [39], σ_2_ = standard deviation of the intervention group and assumed to be 1.46 [40], Δ = difference in group means of the average ST and assumed to be 0.54 [39], Z_1-α/2_ = two-sided Z value (Z = 1.96 for the 95% CI), and Z_1-β_ = power (80%). Hence, n_I_ was 170 participants per arm. Considering a 10% attrition rate due to loss to follow-up and 15% nonresponse or refusal rate, the sample size per arm was calculated as 214.

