## Results

Enrollment of all participants (n=440) was completed during the baseline assessment. The intervention phase could not be started due to restrictions imposed under lockdown to contain the Covid-19 pandemic. Considering the Covid-19 pandemic and likely change in the ST and physical activity of the children, we will measure the ST and physical activity again before delivering the intervention. The intervention was started in November 2020. It will be implemented for 8 weeks. The endline assessment will be done immediately postintervention and after the 6 months of follow-up. The results will most likely be published by 2022.

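### The abstract gives the two-arm total of 428 as the size of each arm, and the sample-size formula as printed gives 175 per arm, not 170

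*Protocol article*

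**What the plan says.** The protocol article gives its size in three places.

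- **Abstract, Methods:** "A sample size of 428 children is estimated per arm".
- **Methods, Phase II, Sample Size:** a two-means formula with unequal variances is used ("The sample size for the individual level randomization was estimated using the following formula"). The inputs are "standard deviation of the control group and assumed to be 2.09", "standard deviation of the intervention group and assumed to be 1.46", a difference in means of 0.54, a two-sided Z of 1.96 and 80% power. The power term is described only by the power itself ("Z_1-β_ = power (80" percent), with no numeric Z value. The result is "Hence, n_I_ was 170 participants per arm". After allowing for 10% attrition and 15% nonresponse or refusal, "the sample size per arm was calculated as 214".
- **Results:** "Enrollment of all participants (n=440) was completed during the baseline assessment".

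The Sampling Technique section adds that consent comes before randomization: only families who agree to take part and to complete the follow-ups are enrolled and allocated.

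**The concern.** The three statements cannot all be true. At 428 per arm the target would be 856, and enrolment that closed at 440 would have reached only about half of it. At 214 per arm the target is 428, and 440 slightly exceeds it. A reader of the abstract alone would believe the trial is twice its planned size, with close to certain power for the assumed difference.

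The figure of 170 also does not follow from the formula printed beside it, and the step from 170 to 214 does not follow from the two loss rates when they are applied as losses. The sample size is a core design figure that others will check or reuse, so it should be reproducible from the text.

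**Working it through.** **Inputs** (Sample Size section): SDs 2.09 and 1.46; difference 0.54; Z for two-sided 5% = 1.96; power 80%, for which the standard normal value is 0.8416. Losses: 10% attrition, 15% nonresponse or refusal. Enrolled: 440 (Results), taken as 220 per arm on the assumption of equal allocation.

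**Step 1. Base size.** n = (SD1² + SD2²)(1.96 + Z)² / 0.54².

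Sum of variances: 2.09² + 1.46² = 4.3681 + 2.1316 = 6.4997. Also 0.54² = 0.2916.

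| Value entered for the power term | n per arm |
|---|---|
| 0.80 | 6.4997 x 2.76² / 0.2916 = 169.79, so 170 (the printed figure) |
| 0.84 | 174.75, so 175 |
| 0.8416 | 6.4997 x 2.8016² / 0.2916 = 174.95, so 175 |

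The printed 170 is reproduced when 0.80 is entered. A one-sided test does not reproduce it (137.8).

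**Step 2. Inflation.** The printed figure first:

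- 169.79 x 1.10 x 1.15 = 214.79, which is 214 if truncated.
- From the rounded 170, 170 x 1.10 x 1.15 = 215.05, and 170 x 1.25 = 212.5.

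So 214 fits multiplying up by the loss rates. Dividing by the retained fractions gives:

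- both losses, from 170: 170 / (0.90 x 0.85) = 222.2, so 223
- both losses, from 175: 175 / (0.90 x 0.85) = 228.8, so 229
- attrition only, from 175: 175 / 0.90 = 194.4, so 195

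**Step 3. Abstract.** 2 x 214 = 428, so 428 is the total for both arms. The enrolled 440 is 12 above that total and 416 below the 856 that 428 per arm would require.

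**Step 4. Power for a difference of 0.54.** Power = Φ(0.54 / √(6.4997/n) − 1.96), with n evaluable per arm.

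| Case | n per arm | Power |
|---|---|---|
| Printed base size | 170 | 78.9% |
| Base size from the formula | 175 | 80.0% |
| 214 less 10% | 192.6 | 83.6% |
| 214 less both losses | 163.7 | 77.3% |
| 220 less 10% | 198 | 84.6% |
| 220 less both losses | 168.3 | 78.5% |
| Abstract's figure, no losses | 428 | 99.2% |

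**The case against.** The strongest reply is that little turns on the calculation. The gap between 170 and 175 is 2.9%, or about one percentage point of power. Refusal happens before randomization, since Study Population makes consent an inclusion criterion and Sampling Technique randomizes only consenting families. It therefore cannot shrink the randomized number. Taken as the number randomized, 214 exceeds the 195 needed for 10% attrition. Enrolment has closed at 440, which gives 84.6% power after that attrition.

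Most of this stands. A reader might infer from Step 2 that 214 fails to cover the stated losses and that the trial is underpowered. The document does not support that as a general statement: the shortfall to about 164 per arm appears only if the 15% is also lost after enrolment.

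The reply does not close the question entirely, because the 15% covers nonresponse as well as refusal and the article does not say when it occurs. Randomization places data collection after allocation. Results reports that baseline was followed by a pandemic delay, with the intervention starting in November 2020 and screen time to be measured again first. Data Management and Analysis drops participants who withdraw before the third week. Each leaves room for loss among families already enrolled.

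A reader might also take it as established that 0.80 was entered in place of the Z value. The arithmetic fits, and so does the wording of the definition, but no Z value for power is printed. It remains an inference.

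None of this touches the abstract, where no reading reconciles 428 per arm with 214 per arm and 440 enrolled.

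**Conclusion.** The point holds, led by the abstract, which overstates the size of each arm by a factor of two and is contradicted by both Sample Size and Results.

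The base figure is also wrong on the printed inputs: 175, not 170. This is a minor error (78.9% against 80% power).

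The inflation uses the wrong operation if both losses apply to enrolled families: 223 or 229 instead of 214, depending on the base. The consequence is conditional. With attrition alone, 214 is enough. With both losses after enrolment, the 440 enrolled fall 18 short of 2 x 229 = 458, and power is 78.5%, about 1.5 points under target.

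These powers rest on the document's own SDs and difference, the normal approximation, and equal allocation of the 440, which is assumed. The errors do not show a materially underpowered trial for the assumed difference.

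**What to change.** 1. In the abstract, give 214 per arm (428 in total), or the restated figure if the calculation is revised.
2. In Sample Size, print Z = 0.842 for 80% power and restate the base size as 175 evaluable per arm.
3. Inflate by division and say which losses fall after randomization: 195 randomized per arm for 10% attrition alone, or 229 if the 15% also applies after enrolment.
4. Report the power of the 440 enrolled under the chosen case, stating the allocation: with 1:1, 84.6% at 198 evaluable per arm, or 78.5% at 168.

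The cost is corrected text only. Design, conduct and analysis are unchanged, and no further enrolment is needed.

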#### Sampling Technique

The list of eligible families (ie, parents who have children aged 2-5 years) will be obtained from the area’s annual health survey report. Families will be randomly selected using the list obtained from the auxiliary nurse midwife. Eligible families providing consent and willing to complete the intervention and follow-ups will be enrolled in the study and randomized into one of 2 groups: control and intervention. The sampling technique and randomization of families using the Consolidated Standards of Reporting Trials (CONSORT) statement is shown in Figure 1 [41].

**Figure 1 figure1:**
[figure not shown]
CONSORT statement flow diagram for the intervention study.

#### Randomization

Computer-generated randomization will be done to select families for the intervention and control arms. However, restricted randomization will be done so that intervention and control groups have a similar number of families from high, middle, and low socioeconomic groups. Geographical differences (urban and slum areas) in the study area will also be considered during randomization to avoid contamination. A computer-generated sequence will be used to allocate the families in the intervention and control groups. The person generating the list of sequences, collecting data, and disseminating the intervention will be the same; hence, concealment might not be possible. Moreover, as the intervention package comprises information, education, and communication material, concealment might not be possible. Data collection and delivery of the intervention will be done only after the family’s allocation in the intervention or control arm.

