#### Data Management and Analysis

Quantitative data from the intervention study will be entered into Microsoft Excel and analyzed using SPSS for Macintosh, Version 25.0 (IBM Corp, Armonk, NY). ST on a weekday and weekend day will be calculated separately as per available literature [47]. So, the average ST (by viewing any type of media gadget) per day in a week will be calculated, and because there are 5 weekdays (Monday to Friday) and 2 weekend days (Saturday and Sunday) in a week, the weighted average ST per day in a week will be calculated as: Average ST per day (minutes) = [(Weekday ST in minutes x 5) + (Weekend ST in minutes x 2)]/7.

Continuous variables will be summarized as means with interquartile ranges and standard deviations. Correlations between a continuous variable and other variables will be estimated. Categorical variables will be summarized as proportions, and differences between groups will be tested using chi square tests. The data will be analyzed as per intention-to-treat analysis (for their initially assigned study arm) and per-protocol analysis. Relative risks and their effect sizes, together with the corresponding 95% CIs, will be estimated. The effectiveness of the intervention will be estimated by calculating the relative risk reduction (1-relative risk). A *P* value <.05 will be considered statistically significant for all analyses.

Information regarding PLUMS will be shared in the first communication and then reinforced every week for 8 weeks. So, participants who withdraw from the trial after the third week will be included in the analysis. Participants who withdraw any time before the third week will be excluded from the analysis.

Caregivers’ knowledge will be analyzed at the end of the intervention if no associations are observed. The proforma on behavior change will be completed at baseline (t_0_) and endline (t_1_) to determine the stage of change the families are at postintervention.

A feedback/compliance questionnaire (Supplementary Table 3 in Multimedia Appendix 5) will be given to the caregivers at each counseling session (weekly) to check their fidelity. The child's fidelity, including the level of engagement, will be checked with personalized journals comprising the activities they performed during the given intervention. The parents will be contacted via their preferred mode of communication weekly to keep them motivated and disseminate the next week's intervention module.

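### Taking urban/slum area into account when allocating individual families balances area between arms but does not prevent contamination, and the article describes no measure of control-arm exposure

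*Protocol article*

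**What the plan says.** Three sections of the protocol article bear on the unit of allocation.

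- **Randomization.** A computer-generated sequence assigns families to the two arms, restricted so that the arms have similar numbers of high, middle and low socioeconomic families. On area it adds: "Geographical differences (urban and slum areas) in the study area will also be considered during randomization to avoid contamination". It does not say how area enters the procedure.
- **Sampling Technique.** Families are drawn at random from a list, and those who consent are randomised to one of two groups.
- **Sample Size.** "The sample size for the individual level randomization was estimated using the following formula". No intracluster correlation, cluster size or design effect appears.

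On analysis, Data Management and Analysis names correlations, relative risks, relative risk reduction and, for categorical variables, this: "Categorical variables will be summarized as proportions, and differences between groups will be tested using chi square tests". No term for socioeconomic group or area is named.

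On exposure, the compliance proforma and the family journals are described as checks on the intervention. The post-intervention assessment repeats the baseline questionnaire in both arms, and none of its listed domains covers receipt of PLUMS material.

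**The concern.** Restricting randomisation by a factor makes the arms alike on that factor. Preventing contamination needs the opposite: the arms must be kept apart in space or social contact. When families are allocated one by one within urban and slum strata, each stratum contains both arms by construction. The article thus credits the design with a protection it does not provide.

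This matters because part of the package can be passed on. Caregivers receive weekly online videos by their preferred means of communication, together with suggested activities and printed material. Any sharing would pull the control mean towards the intervention mean and shrink the estimated effect. A reader of a small or null result would have been told that this route was closed, and would have no data with which to check.

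**Working it through.** **1. Which unit of allocation does the text support?** Sample Size speaks of the individual level, Sampling Technique randomises consenting families, and Randomization uses a sequence that assigns families. The three agree. The only hint of anything else is the purpose attached to area, and the wording there (area is considered) does not say that whole areas are assigned to arms.

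**2. Does the stated sample size fit that reading?** Inputs, all from Sample Size: "standard deviation of the control group and assumed to be 2.09"; "standard deviation of the intervention group and assumed to be 1.46"; "difference in group means of the average ST and assumed to be 0.54"; "two-sided Z value (Z = 1.96 for the 95% CI"); power 80%.

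- Sum of variances: 2.09² + 1.46² = 4.3681 + 2.1316 = 6.4997.
- n = 6.4997 × (1.96 + 0.8416)² / 0.54² = 6.4997 × 7.849 / 0.2916 = 174.9, so 175 per arm.
- The article states that n "was 170 participants per arm", which is within 3% of this. From 170, × 1.25 gives 212.5 and × 1.10 × 1.15 gives 215.05, both close to the stated 214.

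The figure is that of an individually randomised trial with a design effect of 1. It also has no allowance for dilution.

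**3. What could dilution cost?** The article gives no contamination rate, so the loss is an assumption. Results reports 440 enrolled. With an equal split (assumed) and the article's 10% attrition, 440 / 2 × 0.90 = 198 are analysed per arm. Nonresponse is not deducted, because these families are already enrolled.

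Power = Φ( √[198 × (0.54 × (1 − c))² / 6.4997] − 1.96 ), where c is the fraction of the difference lost.

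| c (assumed) | Difference | Power |
|---|---|---|
| 0 | 0.540 | Φ(2.980 − 1.96) = 84.6% |
| 0.10 | 0.486 | Φ(2.682 − 1.96) = 76.5% |
| 0.20 | 0.432 | Φ(2.384 − 1.96) = 66.4% |

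With the stated 170 analysed per arm, the same formula gives 78.9%, 70.0% and 59.8%.

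Here c is the average loss. c = 0.10 means that 10% of controls gain the full effect, or 20% gain half of it.

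**4. What does leaving out the strata do?** If balanced strata explain a share R² of the outcome variance and the test ignores them, the true two-sided error is 2 × [1 − Φ(1.96 / √(1 − R²))]. For R² = 0.05 and 0.10 (both assumed) this is 0.044 and 0.039. The test is mildly conservative. At 170 per arm, adjustment would raise power from 78.9% to 80.9% or 82.9%.

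**The case against.** **Contamination may be slight.** Study Setting gives about 8681 children aged 2-5 years in a zone of 250,000 people. The 440 enrolled are 440 / 8681 = 5.1% of them, so about 2.5% per arm on an equal split. With random sampling this sparse, many control families may have no intervention family nearby. A forwarded video is also not the whole package, which includes an introductory session watched with the lead author, physical books, weekly contact and motivational interviewing as needed. This stands: the 10% and 20% losses illustrate sensitivity, do not predict the result, and may well be high. It does not rescue the stated purpose. Sparse sampling would limit contamination; the use of area in the randomisation would not.

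**A reader might infer that areas were allocated whole**, making this an unacknowledged cluster trial that needs a design effect. The documents do not support that. Three sections describe allocation of families, only two area types are named, and no number or size of areas is given. The flow diagram, which might show how area was used, is not available in the text reviewed.

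**A reader might also infer that the primary analysis wrongly ignores the strata.** The chi-square sentence concerns categorical variables, while the primary outcome is a mean change in minutes. Stratum adjustment is also commonly left to an analysis plan, which is not shown. Adjustment is therefore an improvement to recommend, and its absence from the article is not an error.

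**Conclusion.** The point holds in a limited form. Under the individual allocation that the article describes, taking area type into account does not prevent contamination, so the reason given for using it is wrong. The article also describes no measure of control-arm exposure that would show whether the problem arose. This conclusion rests on the text alone and needs no assumed figure.

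The size of any dilution is unknown. On the stated standard deviations and difference, with 198 analysed per arm, power moves from about 85% to about 76% or 66% if 10% or 20% of the difference is lost. These figures assume an equal split, 10% attrition and the chosen loss fractions.

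It would go too far to say that a null result could not be interpreted. Contamination of this kind biases towards no effect. It would be a limitation to report, and it would not undermine a positive finding.

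**What to change.** 1. In Randomization, state that families are allocated individually, with socioeconomic group (three levels) and area type (urban or slum) as stratification factors. Delete contamination as the reason for using area. Cost: wording only.
2. Adjust the primary screen-time comparison for these two factors. Cost: two covariates, no new data.
3. At the remaining control-arm assessments, add one item asking whether the family has seen or received PLUMS videos, printed material or activities. Report the exposed share and discuss it as a limitation. The intervention began in November 2020 and ran for 8 weeks, so by publication in February 2021 the 6-month follow-up may have been the only assessment left. Cost: one question.
4. Only if whole areas were in fact assigned to arms: say so, model area in the analysis and restate the power, so that Sample Size and Randomization agree.

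None of this requires new participants or a repeat of the randomisation.

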#### Blinding

Blinding will not be possible as the investigator will know the participants in the intervention group because he or she will motivate them to continue the intervention at each step. Also, the participants will know that they are being given an intervention to reduce the ST of their children. However, data entry will be performed by a data entry operator who will be blinded.

#### Stages of the Study

The intervention study will be conducted in 3 stages: baseline assessment, implementation of the intervention, and postintervention assessment.

#### Baseline Assessment

The baseline data were collected from December 2019 to March 2020. During the baseline assessment, the mean ST, prevalence of excessive ST and its correlates, mean duration of physical activity, emotional problems, and sleep disturbances in both the intervention and control arms were measured.

To assess mean ST, physical activity, and prevalence of excessive ST, a pretested, validated, semistructured, bilingual (English and Hindi languages) digital screen exposure questionnaire (DSEQ) was used (Multimedia Appendix 7). The DSEQ was developed in 5 phases. In phase 1, a draft questionnaire was developed by reviewing the literature on existing tools (n=2) from 2009 to 2017. In phase 2, 9 experts assessed the draft Hindi and English questionnaires’ face and content validity. Face-to-face interviews with primary caregivers (n=30) were conducted in a tertiary care hospital for acculturation. In phase 3, a pilot study was conducted among randomly selected families to evaluate the feasibility of the DSEQ in field settings. During phase 4, test-retest reliability was assessed among 30 primary caregivers selected randomly in another urban cluster. In phase 5, the internal consistency of the DSEQ was checked by conducting a cross-sectional study among 400 randomly selected, primary caregivers in Chandigarh, North India. The DSEQ has good internal consistency (Cronbach α=0.73-0.82) and inter-rater agreement (kappa 0.75, 95% CI 0.72-0.78).

The DSEQ was used to collect information from the primary caregivers of the children on (1) sociodemographic profile including family type and socioeconomic status (BG Prasad classification, 2016) [42], (2) digital screen exposure and home media environment, (3) level of physical activity of the child, (4) child’s media-related behaviors, and (5) parental perceptions and literacy regarding digital screen exposure. We recorded the duration and content of media watched by the child on a typical day. The objective criterion to measure ST was the number of hours the child watched a specific TV program. Cinema and movies were excluded from the ST measurement to calculate the actual average of ST for a regular day. Besides, cinema and movies are not watched daily and might falsely increase ST.

We used the 5 progressive physical activity levels among preschoolers given in the Preschool Physical Activity Questionnaire (PrePAQ) to assess physical activity. The PrePAQ categorizes activity into stationery (no action), sedentary (limb or trunk movement), slow-paced (moving easily or slowly), medium-paced (moving at a moderate pace), and fast-paced (quick pace or hard effort) [43].

The standard Preschool Child Behavior Check List was used to assess the child’s emotional and behavioral development. It has been validated in an Indian setting and has the right internal consistency (Cronbach α=0.95) [44]. It consists of 100 items with a 3-step response scale (0, 1, and 2). These items are scored as being absent (score, 0), occasionally present (score, 1), and very often present (score, 2).

The sleep disturbances scale for children was used to measure the child’s sleep patterns. It is a 26-item Likert-type scale that measures specific sleep disorders along with overall sleep disturbances in children. It has been validated and has an internal consistency of 0.71-0.79, test-retest reliability of 0.71, and diagnostic accuracy of 0.91 [40].

The lead author visited the homes of the study families and conducted face-to-face interviews during the baseline assessment.

